## Abstract

**Introduction:**

Strict imaging surveillance protocols to detect complications following endovascular aneurysm repair (EVAR) are common practice. However, controversy exists as to whether all EVAR patients need intense surveillance. The 2019 European Society for Vascular Surgery guidelines for management of abdominal aortic aneurysm (AAA) suggest that patients may be considered for limited follow-up with imaging if classified as ‘low risk’ for complications based on their initial postoperative imaging. The current study aims to investigate the intervention-free survival and overall survival stratified for patients with and without yearly imaging surveillance.

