**Methods and analysis:**

The Observing a Decade of Yearly Standardised Surveillance in EVAR patients with Ultrasound or CT Scan study comprises a national multicentre retrospective cohort study in 17 medical centres. Consecutive patients with an asymptomatic or symptomatic infrarenal AAA who underwent EVAR between January 2007 and January 2012 will be included in this study with follow-up until December 2018. Clinical variables and all follow-up information will be retrieved in extensive data collection from the patient’s medical records. In addition, an e-survey was sent to vascular surgeons at the 17 participating centres to gauge their opinions regarding the possibility of safely reducing the frequency of imaging surveillance. Primary endpoints are intervention after EVAR and aneurysm-related mortality. The initial estimated sample size is 1997 patients.

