### Background and relevant literature and data

Before initiating the ODYSSEUS study, we conducted a survey among Dutch vascular surgeons to find out if they support the possibility of reducing the frequency of imaging surveillance. In this survey, vascular surgeons reported the main reasons patients did not comply with follow-up visits, that is, they had forgotten the appointment or were prevented by force majeure. Most physicians estimated that less than 10% of their patients had missed one or more follow-up visits post-EVAR. This might be an overestimation of the true adherence to follow-up visits, as these observations are in contrast with a study reporting that only 43% of patients had complete surveillance.^4^

We also asked participating vascular surgeons to upload their standard post-EVAR protocol to investigate if there were differences between centres in the Netherlands. In all centres, imaging took place within the first 3 months after surgery, mostly by CTA. Most centres comply with their own post-EVAR surveillance protocols which have many commonalities with the SVS and ESVS guidelines. Only one centre uses precisely the same post-EVAR surveillance protocol as recommended by the SVS guidelines. Another centre had already reduced follow-up imaging to once every 5 years, using either CTA or DUS as is stated in the new ESVS guidelines.^3^ While vascular surgeons still seem to adhere to their hospital-specific protocol, they do support the need for reducing follow-up by selecting a group of patients for which yearly follow-up can safely be omitted. However, some surgeons indicated that more evidence is needed than is available in the current literature.^6 7^

In studies that have investigated the indications for post-EVAR intervention, it is stated that 61%–98% of interventions were necessary because of symptoms and not because of findings at surveillance imaging. This suggests that post-EVAR surveillance protocols provide no benefit to a large group of patients, as complications occur in between surveillance visits.^8 9^ Imaging surveillance may even lead to unnecessary interventions and it does not appear to be associated with improved survival.^9 10^ We hypothesise that the requirement for routine imaging for patients at low risk can be reduced. However, novel endovascular devices still require more intensive surveillance as the short- and long-term results of those devices remain undetermined.

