## Study objectives

The objective of this study is to evaluate whether imaging surveillance frequency might have been safely reduced in a selected group of EVAR patients, for example, in patients with an asymptomatic or symptomatic infrarenal AAA who underwent EVAR and who had no abnormalities on the 3-month postoperative CTA. The clinical course of a large cohort of patients will be evaluated with follow-up ranging between 6 and 11 years. Baseline patient characteristics, aortic anatomy and details of the operation will be derived from the patient’s medical record. The first milestone during follow-up is the first postoperative CTA. This scan either shows complications such as endoleaks, malposition or migration of the graft, or the absence thereof. All follow-up visits, imaging studies, as well as all interventions after EVAR and outcomes will be registered. Our hypothesis is that patients with less follow-up will have better outcomes regarding the number of interventions and aneurysm-related mortality compared to patients with annual follow-up. Regarding the intervention rates, it is expected that adherence to imaging surveillance may detect more abnormalities triggering re-interventions which in itself may cause additional complications and perhaps even a decrease in survival rates. We hypothesise that the need for routine imaging for patients with no abnormalities at their initial CTA can be decreased.

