**Figure 1 F1:**
[figure not shown]
Patient subgroups. AAA, abdominal aortic aneurysm; CTA, CT angiography; EVAR, endovascular aneurysm repair.

The standard of care is defined by the current guidelines and IFU. The usual follow-up schedule in the IFU is: CTA and abdominal X-ray at 30 days, 6 and 12 months and yearly thereafter. The 2019 ESVS guidelines recommend a CTA 30 days after EVAR. If there is adequate seal and no endoleak, patients are classified as low risk and CTA follow-up may take place 5 years later. If there is an inadequate seal and endoleak type I/III patients could be either evaluated for re-intervention or if sac shrinkage occurs yearly DUS is recommended. In the 2018 SVS guideline, CTA at 1 and 12 months is recommended and if neither endoleak nor sac enlargement is documented, DUS is suggested for annual postoperative surveillance. In our study design, the definition of compliance is undergoing imaging surveillance every 16 months since patients in most centres will be rescheduled if they missed their annual follow-up visit. Device-specific complications after EVAR will also be examined.

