### Study procedures

The primary outcomes of this study are interventions and aneurysm-related mortality for patients who had a normal initial postoperative CTA and who do adhere to our definition of yearly imaging surveillance over a 6-year to 11-year follow-up period, compared to those who do not adhere to our definition.

Interventions are EVAR-related interventions defined by the SVS reporting standards as postoperative adjunctive manoeuvres.^16 17^ Interventions for wound complications at the access site are not included, since these are detectable without the use of imaging.

Date of death during follow-up, if applicable, will be obtained from patient medical records and verified by the Dutch municipal personal records database (GBA).

Details of all surveillance imaging are obtained from patient medical records and radiology reports. The time between imaging appointments is calculated to determine whether patients adhere to this studies definition of with yearly imaging surveillance, that is, within every 16 months.

Date, type, indication and outcome of all postoperative imaging during follow-up are obtained from patient medical records, specifically imaging order forms and radiology reports. A normal initial postoperative CT scan is defined as a CT scan which shows no endoleaks, endograft migration (>10 mm), kinking or obstruction. All imaging outcomes are based on the report compiled by radiologists. These reports will not be re-evaluated by an independent radiologist, since we want to base our outcomes on real life data.

Secondary outcomes are all-cause mortality, type I, type II, type III and type IV endoleak, graft or outflow (iliac) occlusion, aneurysm rupture and endograft infection. This is also obtained from patient medical records, specifically radiology reports and Dutch municipal personal records database (GBA).

Date of aneurysm rupture is obtained from patient medical records, specifically operative reports, radiology reports and progress notes.

Costs of all EVAR-related imaging and outpatient clinic visits will be calculated per patient. Cost is defined as volume times price. Prices from the ‘Cost manual of the Dutch Health Care Institute’’ will be used. Costs for the patients will also be included. The quality-adjusted life years, a generic measure of disease burden including both the quality and quantity of life, cannot be calculated with this retrospective design.

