### Statistical methods

Differences in baseline characteristics between patients undergoing or not undergoing yearly standardised imaging surveillance by either CTA or DUS, will be analysed using the χ^2^ or Fisher's exact test for categorical variables and the student's t-test or Mann-Whitney test for continuous variables, if appropriate.

The primary endpoints, that is, survival and freedom from intervention will be estimated by Kaplan-Meier survival analysis and differences between groups will be assessed with the log-rank test.

Secondary endpoints such as freedom from aneurysm rupture between patients with and without yearly standardised imaging surveillance will be estimated by Kaplan-Meier survival analysis, and differences between these groups will be calculated with the log-rank test.

Multivariable cox regression analysis will be used to determine survival and the freedom of intervention corrected for age, gender, AAA diameter, ASA classification, neck length, neck angulation and type of endograft. The association between postoperative intervention and the following covariates will be investigated with the multivariate Cox-regression analysis:

Age.Gender.AAA diameter.ASA classification.Neck length (>15 mm).Neck angulation (>60°).Type of endograft.Initial postoperative CTA.

All statistical analyses will be done with SPSS software (IBM, V.25). The level for statistical significance is set at a p value <0.05. The proportion of missing data will be displayed. The missing values will be imputed by multiple imputation techniques if this does not exceed 10%–15% and conduct a sensitivity analysis to investigate the effect of the missing data on the results of the analysis. If missing data on outcome variables exceeds 15%, we plan to perform subgroup analysis.

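### Overall survival is compared by imaging attendance and read as a possible imaging effect, with nothing described to show whether adjustment removes attender selection; non-aneurysm death would be a cheap negative control

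*Protocol article*

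**What the plan says.** The Abstract (Introduction) sets out to "investigate the intervention-free survival and overall survival stratified for patients with and without yearly imaging surveillance". Under Statistical methods, in the sentence on the primary endpoints, "survival and freedom from intervention will be estimated by Kaplan-Meier survival analysis and differences between groups will be assessed with the log-rank test". The same section adds that "Multivariable cox regression analysis will be used to determine survival and the freedom of intervention", corrected for age, gender, AAA diameter, ASA class, neck length, neck angulation and endograft type.

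Groups A and B both have a normal first CTA and differ only in whether imaging was yearly. The text under Figure 1 says that "the definition of compliance is undergoing imaging surveillance every 16 months", and Study procedures works this out from the intervals between imaging appointments.

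The Study objectives give survival a causal reading: imaging may trigger re-interventions that "may cause additional complications and perhaps even a decrease in survival rates". On why visits were missed, the surgeons surveyed in the Background section answered that "they had forgotten the appointment or were prevented by force majeure".

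The status of survival is not consistent. The Abstract states "Primary endpoints are intervention after EVAR and aneurysm-related mortality", and Study procedures states "Secondary outcomes are all-cause mortality". Statistical methods calls survival primary without saying which survival.

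**The concern.** Patients who keep coming for scans over 6 to 11 years may differ in fitness and behaviour from those who do not. Imaging of the aneurysm can prevent only aneurysm-related deaths. If these are a small part of all deaths, overall survival by attendance group is mostly a comparison of deaths that imaging cannot prevent, and it responds to any difference between the kinds of patient in the two groups.

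A survival difference might then be credited to surveillance, or blamed on it, when it reflects selection. The same selection can act on aneurysm-related mortality, where there are too few events for it to show. That endpoint carries the non-inferiority claim meant to inform less intensive follow-up. The limitations in the Discussion name attrition, transfer between centres and changing practice, but not selection by who attends.

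**Working it through.** **Inputs from the article (Sample size and power).** 719 patients per group, 1438 in total; 5% aneurysm-related mortality at 7 years. The text words the 5% the wrong way round, but the accompanying 0.95 makes the meaning clear.

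**Assumed, not in the article.** All-cause mortality M at 7 years of 20% to 60%; attender hazard ratios (HR) for non-aneurysm death of 0.90 and 0.80; equal groups; proportional hazards.

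**1. The article's own figures.**
- Interventions, two-sided 0.05, 90% power: (1.960 + 1.282)² × (0.75×0.25 + 0.82×0.18) / 0.07² = 718.6, so 719. This matches.
- Non-inferiority, one-sided 0.05, 80% power: (1.645 + 0.842)² × 2×0.95×0.05 / 0.03² = 652.6, so 653. This matches, so 5% is the rate used; the 0.97 also printed there would give 400.
- No power is stated for overall survival.

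**2. Share of deaths that are not aneurysm-related.** This is 1 − 0.05/M. It passes one half when M exceeds 10%.

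**3. Chance of a significant survival log-rank with no imaging effect.** Let f = 0.05/M and apply the attender HR to non-aneurysm deaths only:
- overall HR = f + (1 − f) × HR
- attenders' mortality = 1 − (1 − M)^(overall HR)
- deaths D = 719 × (M + attenders' mortality)
- chance = Φ(|ln overall HR| × √(D/4) − 1.96)

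Example, M = 40% and HR 0.80: f = 0.125; overall HR = 0.125 + 0.875×0.80 = 0.825; attenders' mortality 34.4%; D = 535; chance = Φ(0.1924 × 11.57 − 1.96) = Φ(0.265) = 60%.

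**4. Power for a real imaging effect.** If imaging halved aneurysm-related deaths, overall HR = 1 − f/2. At M = 40% this is 0.9375 on 1438 × 0.40 = 575 deaths: Φ(0.0645 × 11.99 − 1.96) = 12%.

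**5. Power of the proposed control.** Non-aneurysm deaths are about 1438 × (M − 0.05), put into the same power formula.

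| M (assumed) | Non-aneurysm share | No imaging effect, HR 0.90 | No imaging effect, HR 0.80 | Imaging halves aneurysm deaths | Non-aneurysm deaths | Control's power at HR 0.85 | Control's power at HR 0.80 |
|---|---|---|---|---|---|---|---|
| 20% | 75% | 10% | 26% | 20% | 216 | 22% | 37% |
| 30% | 83% | 14% | 45% | 15% | 360 | 34% | 56% |
| 40% | 87.5% | 19% | 60% | 12% | 503 | 45% | 71% |
| 50% | 90% | 24% | 73% | 10% | 647 | 54% | 81% |
| 60% | 92% | 29% | 82% | 9% | 791 | 63% | 88% |

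Putting attenders at 43% instead of half (the complete-surveillance figure cited in the Background) moves the no-imaging-effect columns by less than one percentage point. Aneurysm-related deaths number about 1438 × 0.05 = 72 throughout.

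**The case against.** The strongest reply is that this asks for an added analysis and exposes no error, and that a condensed article may leave sensitivity analyses to a fuller plan. That limits the weight of the point but does not remove it. The article itself fixes the survival comparison, the attendance-based groups and the causal reading, and describes nothing that tests whether the adjustment works.

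Several further replies stand:

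- A reader might infer that the plan has no safeguard. It has two partial ones: the Cox model includes age and ASA class, and aneurysm-related mortality is a separate endpoint.
- A reader might infer that the 5% figure alone proves most deaths are unrelated to the aneurysm. It does not; an all-cause rate is needed, and none is given.
- The percentages above are for the unadjusted log-rank test. The residual effect after adjustment is unknown, and the hazard ratios have no source in the article.
- Forgotten appointments and force majeure are surgeons' impressions and do not show frailty. The Background also reports different centre protocols, one already imaging every 5 years, so group B reflects centre policy as well as patient behaviour.
- A fitter-attender effect favours yearly imaging and so works against the study's hypothesis. Bias can also run the other way: sicker patients may be imaged more, and early deaths may count as compliant because there was no time to miss a 16-month interval. That direction would favour less imaging and could produce false non-inferiority.
- The control is imperfect. Its power at HR 0.85 is only 22% to 63%, and the CTA harms named in the Introduction (cancer, nephropathy) could mask a fitter-attender effect.

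**Conclusion.** A cheap improvement, not a fatal flaw. For any all-cause mortality above 10% at 7 years, overall survival by attendance group is mostly non-aneurysm death. Across the assumed 20% to 60%, the share is 75% to 92%. At an attender HR of 0.80, selection alone gives a significant unadjusted log-rank in 26% to 82% of studies, more often than halving aneurysm-related deaths would (9% to 20%). At HR 0.90 the figure is 10% to 29%.

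It is tempting to say that even a modest attender effect will be taken for an imaging effect. The HR 0.90 figures, the planned adjustment and the unknown net direction of bias do not support that; it may happen. What is supported is narrower: overall survival by group should not be attributed to imaging without a check that the article does not describe. All of this rests on the assumed mortality and hazard ratios, proportional hazards and equal groups.

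**What to change.** In Statistical methods:

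- Prespecify death not related to the aneurysm as a negative-control outcome for group A against group B, with the same covariates and time zero as the mortality analysis.
- Report its adjusted hazard ratio and 95% confidence interval beside aneurysm-related and all-cause mortality.
- Interpret it in both directions. After a clear difference either way, report the A against B mortality results, including non-inferiority, as probably affected by selection or by how exposure was classified, and do not attribute overall survival to imaging. A one-sided pass or fail rule would miss bias against yearly imaging.
- State that a null result does not show that bias is absent, and name the CTA harms as a limit of the control.
- Say whether survival in the primary-endpoint sentence means overall or aneurysm-related survival, and reconcile it with the Abstract, the Main study endpoint and Study procedures.

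The cost is one extra Cox model. Date of death is already collected and verified, and aneurysm-related status is needed for the primary endpoint anyway. The downside is that the mortality conclusion may have to be more limited.

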**Methods and analysis:**

The Observing a Decade of Yearly Standardised Surveillance in EVAR patients with Ultrasound or CT Scan study comprises a national multicentre retrospective cohort study in 17 medical centres. Consecutive patients with an asymptomatic or symptomatic infrarenal AAA who underwent EVAR between January 2007 and January 2012 will be included in this study with follow-up until December 2018. Clinical variables and all follow-up information will be retrieved in extensive data collection from the patient’s medical records. In addition, an e-survey was sent to vascular surgeons at the 17 participating centres to gauge their opinions regarding the possibility of safely reducing the frequency of imaging surveillance. Primary endpoints are intervention after EVAR and aneurysm-related mortality. The initial estimated sample size is 1997 patients.

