### General study design

A multicentre retrospective cohort study in 17 medical centres in the Netherlands. Data will be collected from the medical records of all consecutive patients with AAA who underwent EVAR between January 2007 and January 2012. This selection provides a theoretical length of follow-up of 6–11 years on December 2018. Patients will be divided into three groups: (A) patients without abnormalities at their first postoperative CTA with yearly imaging surveillance, (B) patients without abnormalities at their first postoperative CTA without yearly imaging surveillance and (C) patients with abnormalities at their first postoperative CTA (figure 1). This retrospective design has the advantage of collecting long term follow-up data. The Dutch Dream trial found that the number of interventions starts to rise 4 years after EVAR and the long-term results of the EVAR-1 trial show that EVAR has an early survival benefit but inferior late survival compared to open surgical repair.^13 14^ This is in contrast to the recently published long-term results of the OVER trial in which no difference was observed between EVAR and OSR in the primary outcome of all-cause mortality.^15^ Hence, a prospective study would take approximately 8 to 10 years to gather enough patients with adequate follow-up.

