### Study population

Patients eligible for this retrospective study are all adults who underwent elective EVAR for asymptomatic or symptomatic infrarenal AAA between January 2007 and January 2012. Table 1 gives a more detailed overview of the inclusion and exclusion criteria.

**Table 1 T1:** Retrospective cohort

Inclusion criteria	Exclusion criteria
Age ≥18 years	Connective tissue disease
Patient with an (a)symptomatic infrarenal abdominal aortic aneurysm EVAR between January 2007 and January 2012	Patients who objected to their retrospective data being used
Patients with an initial postoperative CTA within 90 days after EVAR	

CTA, computed tomography angiography; EVAR, endovascular aneurysm repair.

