### Primary and secondary endpoints

#### Main study endpoint

The number of patients with an intervention and aneurysm-related mortality classified for patients with and without yearly imaging surveillance.

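### As written, the intervention endpoint runs from EVAR, so interventions before the normal CTA that admits a patient to the A v B comparison count as primary events

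*Protocol article*

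**What the plan says.** The abstract (Methods and analysis) states: "Primary endpoints are intervention after EVAR and aneurysm-related mortality". The Main study endpoint section gives "The number of patients with an intervention and aneurysm-related mortality classified for patients with and without yearly imaging surveillance", with no start date.

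Study procedures defines the event: "Interventions are EVAR-related interventions defined by the SVS reporting standards as postoperative adjunctive manoeuvres". It names one exclusion: "Interventions for wound complications at the access site are not included, since these are detectable without the use of imaging".

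On timing:
- Study objectives: "All follow-up visits, imaging studies, as well as all interventions after EVAR and outcomes will be registered".
- General study design, referring to the period in which EVAR was performed: "This selection provides a theoretical length of follow-up of 6–11 years on December 2018".
- Study objectives: "The first milestone during follow-up is the first postoperative CTA". Follow-up has therefore begun before that scan.

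On eligibility, Table 1 (Study population) requires "Patients with an initial postoperative CTA within 90 days after EVAR". General study design and Study procedures confine the primary comparison to patients whose first CTA is normal: group A with yearly imaging, group B without. Patients with an abnormal first CTA form group C. Statistical methods plans Kaplan-Meier curves and log-rank tests for freedom from intervention and names neither a time zero nor a landmark.

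**The concern.** Event counting starts at the operation, but membership of A or B is settled only by a scan up to 90 days later. Take a patient who has an EVAR-related intervention soon after surgery for a problem found without CTA, and whose first CTA is then normal. That patient enters A or B with the primary event already recorded, before there was any surveillance schedule to follow.

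This sits badly with the protocol's own reasoning in three ways:
- Wound procedures are dropped because surveillance imaging plays no part in finding them. An intervention before the first scan is equally outside the reach of the schedules being compared.
- Study objectives explains the expected excess of interventions under adherence by abnormalities that surveillance detects. An intervention before the first scan cannot arise that way.
- The two primary endpoints are treated differently. A patient must be alive to have the qualifying CTA, so no earlier death can count in A v B, yet an earlier intervention can.

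Two things are at stake. Irrelevant events dilute the contrast, and each one uses up that patient's first event, so a later intervention of real interest is lost. If the events are also unevenly spread between A and B, part of the observed difference has nothing to do with surveillance.

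**Working it through.** **1. The plan's own figure.** Inputs from Sample size and power: 75% v 82% intervention-free at 7 years, 90% power, significance level 0.05 (two-sided fits).

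n = (1.960 + 1.282)² × (0.75×0.25 + 0.82×0.18) / 0.07² = 718.6 (unrounded normal quantiles), so 719 per group, as stated. The pooled-variance formula gives 722. The sample size reproduces, and the point concerns only what is counted.

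**2. Inputs the documents do not give (assumptions).**
- e: share of A and B patients with an intervention before the initial CTA.
- s: share of those patients who end up in A.
- Share intervention-free after the CTA under no true difference: 80% in both groups, whether or not there was an early intervention.
- 719 per group, compared as two proportions.

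**3. Equal early rates.** Apply the planned 75% and 82% after the CTA and add 2% early events to each group:
- A: 0.75 × 0.98 = 73.5%. B: 0.82 × 0.98 = 80.4%. Difference 6.9 points.
- Power at 719 per group is 87.1%, against 89.9% without early events.
- With no true effect there is no spurious gap, and the false-positive rate stays at 5%.

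**4. Unequal early rates, no true effect.** With equal groups, eA = 2es and eB = 2e(1 − s). The spurious gap in intervention-free rates is 0.80 × (eA − eB). For e = 3%:

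| s | eA | eB | eA − eB | Gap in 7-year rates |
|---|---|---|---|---|
| 50% | 3.0% | 3.0% | 0 | 0 |
| 60% | 3.6% | 2.4% | 1.2 points | 1.0 point |
| 70% | 4.2% | 1.8% | 2.4 points | 1.9 points |
| 80% | 4.8% | 1.2% | 3.6 points | 2.9 points |

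The factor 0.80 is needed because one in five of these patients would have had a later intervention anyway.

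**5. Effect on the test, more extreme splits, no true effect.**

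| Early rate, A v B | Gap | Chance of a significant result |
|---|---|---|
| 1% v 0% | 0.8 points | 6.6% |
| 2% v 0% | 1.6 points | 11.6% |
| 4% v 0% | 3.2 points | 31% |

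**6. If the planning rates already contain early events.** Removing 2% from A and none from B gives 0.75/0.98 = 76.5% v 82.0%, a difference of 5.5 points, with 73% power at 719 per group. Removing 2% from both gives 76.5% v 83.7%, a difference of 7.1 points, with 92% power.

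**The case against.** The strongest reply is that the text never states a time zero. The abstract's phrase may only name a type of event, the sentence on registering interventions concerns data collection, and the 6-11 years are called theoretical. A journal article may leave the origin of a Kaplan-Meier curve to the full protocol or analysis plan, and the cited reporting standards, which are not at hand, may set a perioperative boundary. It is true that inclusion of pre-CTA events follows from the combined wording and not from an express statement. But the article does more than stay silent: it names the event by reference to EVAR, dates follow-up from EVAR, places the first CTA inside follow-up and lists one exclusion that does not reach these events. Followed as written, it counts them.

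The second reply is that few patients are affected, and this largely stands. Study procedures classes a CTA showing endoleak, migration, kinking or obstruction as abnormal, so a complication first seen on an early CTA sends the patient to group C. Only problems found without CTA, treated, and followed by a normal first CTA reach A or B. The window is at most 90 days of a 7-year endpoint.

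The third reply concerns direction. A reader might infer that these events gather in the yearly-imaging group, because early trouble invites closer imaging, and so favour the hypothesis of fewer interventions with less follow-up. The documents neither state nor exclude this. Adherence means imaging at least every 16 months, which extra scans in the first weeks do not secure, and the surveyed surgeons attributed missed visits to forgotten appointments and force majeure. The direction remains a possibility only.

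**Conclusion.** The mismatch is real: the event clock starts at EVAR, entry to A v B is settled at the CTA, and nothing removes EVAR-related interventions in between. The certain consequence is modest dilution and the loss of some later first events, about 3 points of power if 2% of each group are affected. A spurious gap arises only if early interventions are unequally spread. It is about 1.0-2.9 of the planned 7 points for a 3% early rate with 60-80% in A and 80% intervention-free after the CTA. All of these inputs are assumptions.

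Three stronger readings are not supported. It is not every intervention that counts, since access-site wound procedures are excluded. A systematic bias against yearly imaging is not shown. Nor may the 1.2-3.6 point differences in early-event rates be read as gaps in 7-year rates, which would put the error at up to half the planned effect, because some of these patients would have had a later event anyway. Aneurysm-related mortality is not affected. The change is worth making because it is cheap and removes the ambiguity, not because the likely error is large.

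**What to change.** For the A v B comparison:
- Set time zero at the date of the initial normal CTA, count interventions from that date, and measure 7-year freedom from intervention from it.
- Report interventions before that CTA separately, by group, and do not count them as primary events.
- Enter intervention before the first CTA (yes/no) as a baseline covariate in the Cox model for freedom from intervention.

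This changes analysis wording only, because the dates of imaging and of interventions are already collected under Secondary study endpoints. The price is that a few early events and up to 90 days of follow-up leave the primary comparison. It does not cure the separate problem that adherence is defined by imaging carried out after time zero.
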